### Data collection and management

2.8

Source data will be collected using electronic case report forms within a secure, web-based Electronic Data Capture (EDC) system. Site investigators will be responsible for data entry. All study personnel will receive standardized training on the study protocol and data entry procedures.

Data management will be facilitated by a multi-center research collaboration platform - a validated EDC system hosted by Beijing Bioknow Information Technology Co., Ltd. This platform provides secure data collection, tracking, validation, and export functionalities.

Two independent clinical research coordinators will perform double data entry. The EDC system will then compare entries for verification. Following this, investigators will review and confirm the data. All data changes will be logged in the system’s audit trail. Participants will be identified by unique codes to ensure confidentiality. The principal investigator will bear overall responsibility for data integrity.

An independent Data Monitoring Committee (DMC) will periodically review data quality and safety, which empowered to recommend modifications to the trial (dose adjustment, sample size re-estimation) based on interim analyses of accrued data. The study database will be locked after resolving all data queries and completing final participant follow-up.

### Statistical analysis

2.9

All analyses will be performed using SAS software (version 9.4). Efficacy analyses will be conducted on both the Full Analysis Set (intention-to-treat principle) and the Per-Protocol Set. Safety analyses will be performed on the Safety Set. Prespecified subgroup analyses based on randomization stratification factors, and multivariable adjustment will be used to minimize the influence of treatment heterogeneity. Time-to-event endpoints (EFS, DFS, OS) will be summarized using Kaplan-Meier survival curves and compared between groups using the log-rank test. The Cox proportional hazards model will be employed for multivariate analysis to adjust for potential confounding variables. All statistical tests will be two-sided, with a *p*-value < 0.05 considered statistically significant.

Subgroup analyses: To explore potential beneficiary characteristics, we will perform prespecified subgroup analyses according to baseline clinical factors (age, sex, tumor clinical stage, T stage, N stage, PD-L1 CPS, MSI/MMR status, chemotherapy regimen, immunotherapy use, baseline Karnofsky score, TCM syndrome classification, and relevant biomarker subgroups). For each subgroup, the treatment effect on EFS will be estimated, and interactions between treatment and subgroup factors will be tested using the Cox model. The model selection strategy will be forced entry of these pre-specified variables (no stepwise selection) to avoid overfitting and multiplicity issues. Proportional hazards assumption will be tested using Schoenfeld residuals. These analyses are exploratory and hypothesis-generating; no adjustment for multiple testing will be applied. This study is not powered for formal predictive model development or validation.

Multiple correction strategy: To control the type I error rate due to multiple secondary endpoints, we will apply a hierarchical testing procedure. The primary endpoint EFS will be tested first at α=0.05 (two-sided). Only if the primary endpoint is statistically significant will secondary efficacy endpoints (OS, DFS, 1-/2-/3-year recurrence/metastasis rates) be tested sequentially using a fixed-sequence procedure to preserve the overall α level. If the primary endpoint is not statistically significant, all secondary endpoints will be considered exploratory and reported descriptively without formal hypothesis testing. All other secondary endpoints (postoperative complications, symptom burden, TCM symptoms, immunological biomarkers, and serum tumor markers) will be reported descriptively with nominal *p*-values. These analyses are hypothesis-generating and will not be subject to formal multiplicity adjustment. Results will be interpreted with appropriate caution.

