### Randomization method

2.3

The blinded document (Participant Randomization Table and Drug Assignment Table) of this trial is generated by unblinded statistician using SAS software (Version 9.4) and uploaded to the central randomization system by the randomization system administrator (provided by Beijing Bio-Thera Information Technology Co., Ltd). SAS software was used to generate random numbers and treatment groups corresponding to random numbers. Parameters such as procedure, seed number, block length during randomization were kept in an unblinded folder and the randomization table was reproducible. These persons were not involved in participant recruitment, treatment, or outcome assessment. The central randomization system will complete the assignment of participant randomization number and drug management during the trial. This trial was stratified by neoadjuvant chemotherapy ± immunotherapy using stratified block randomization. Authorized study personnel at each participating site performed subject assignment via the randomization system after confirming eligibility and obtaining informed consent. The grouping process was done automatically by a centralized system and did not rely on the subjective judgment of the researcher.

To ensure data confidentiality and prevent unauthorized access, the randomization system maintains a complete electronic audit trail documenting all allocation-related activities, including login attempts, randomization requests, data entries, and emergency unblinding, with timestamps and user identification. Access to the randomization module is strictly role-based, with different authorization levels assigned to investigators, study coordinators, statisticians, and system administrators. The integrity of the allocation process is further overseen by independent clinical monitors. The randomization schedule itself remains sealed and inaccessible to all study personnel until database lock, except for emergency unblinding.

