### Sample size calculation

2.5

This is a randomized, placebo-controlled superiority trial with a 1:1 allocation ratio. The primary endpoint is EFS. Based on the KEYNOTE-585 trial results (11), the assumed 3-year EFS rate for the control group (receiving perioperative chemotherapy ± immunotherapy) is 44%. We hypothesize that the addition of SQFWG will increase the 3-year EFS rate by 20% (absolute improvement), resulting in a rate of 64% for the experimental group. Using a two-sided significance level (α) of 0.05 and a power (1-β) of 80%, and assuming a constant accrual rate over an enrollment period of 36 months, the sample size was calculated using PASS software (version 15). This calculation yielded 114 participants per group. To account for an estimated 20% dropout rate, the final target enrollment is set at 143 participants per group. The design is event-driven, requiring a sample size of 286 cases. The duration of enrollment is 3 years, and the total study duration is 5 years, taking into account a 20% dropout rate.

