### Interventions

2.6

Experimental Group: Participants will receive SQFWG, composed of *Astragalus membranaceus* (Huangqi), *Codonopsis pilosula* (Dangshen), *Atractylodes macrocephala* (Baizhu), *Gallus domesticus* (Jineijin, endothelium corneum of chicken gizzard), stir-fried *Hordeum vulgare* (Chao Maiya), stir-fried *Setaria italica* (Chao Guya), *Glycyrrhiza uralensis* (Gancao), and other herbs in specified ratios, in addition to the perioperative therapy. The granules will be administered orally at a dose of one packet three times daily, dissolved in hot water and taken after meals. Each treatment cycle is 3 weeks, synchronized with the chemotherapy schedule. Administration will continue concurrently with perioperative therapy until disease progression, unacceptable toxicity, or completion of the prescribed therapy. For patients undergoing surgery, oral administration will resume postoperatively based on recovery status.Control Group: Participants will receive a matched placebo in addition to the perioperative therapy. The placebo is designed to be indistinguishable from the active granules in outer packaging, dosage form (color, shape), and taste. Its composition includes: SQFWG extract powder (5%, sub-therapeutic dose), maltodextrin, a bitter flavoring agent, sucralose, yellow dextrin, and brown dextrin. Maltodextrin and sucralose conform to the standards for pharmaceutical excipients as per the Chinese Pharmacopoeia (2025 Edition, Volume IV). The bitter flavoring agent, yellow dextrin, and brown dextrin are food-grade additives compliant with national food safety standards. The dosing regimen (dose, frequency, and route) is identical to that of the experimental group.Perioperative Therapy (Both Groups): Participating centers will follow unified protocol-specified perioperative treatment principles based on contemporary CSCO and international guidelines. Based on the results of the KEYNOTE-585 (11) and RESOLVE (7) trials, the primary chemotherapy regimens are limited to SOX or XELOX. The preoperative phase will consist of 2–4 cycles of neoadjuvant SOX or XELOX chemotherapy, with or without immunotherapy. Postoperatively, participants will receive 4–6 cycles of adjuvant SOX chemotherapy (which may be followed by S-1 monotherapy) or 4–6 cycles of XELOX chemotherapy, with or without immunotherapy. Treatment will continue until disease progression, unacceptable toxicity, or completion of the planned cycles. The specific immunotherapy regimen is not restricted by the protocol. Immunotherapy (e.g., pembrolizumab, durvalumab, camrelizumab, or other PD-1/PD-L1 inhibitors) is permitted only for patients with biomarker evidence of potential benefit (e.g., PD-L1 CPS ≥5, MSI-H, or EBV positivity) based on current guidelines. The choice of agent is at the investigator’s discretion, the specific agent, number of cycles, and timing must be documented, but not restricted to reflect real-world practice.① Chemotherapy regimens:SOX regimen (3-week cycle): Oxaliplatin 130 mg/m², administered intravenously over 2 hours on Day 1; S-1 40–60 mg (based on body surface area: <1.25 m²: 40 mg; 1.25–1.5 m²: 50 mg; >1.5 m²: 60 mg), taken orally twice daily after meals on Days 1–14, followed by a 7-day treatment-free interval.XELOX regimen (3-week cycle): Oxaliplatin 130 mg/m², administered intravenously over 2 hours on Day 1; Capecitabine 1,000 mg/m², taken orally twice daily on Days 1–14, followed by a 7-day treatment-free interval.② Immunotherapy regimens:Pembrolizumab: 200 mg administered intravenously over 30 minutes on Day 1 of each 3-week cycle.Durvalumab: 1,500 mg administered intravenously over 60 minutes on Day 1 of each 4-week cycle.Camrelizumab or Sintilimab: Administered per standard institutional protocols at approved doses (typically 200 mg Q3W for Camrelizumab; 200 mg Q3W for Sintilimab).The protocol specifies the recommended dosing schedules for commonly used PD-1/PD-L1 inhibitors administered according to the approved product labeling and current clinical guidelines. The duration of immunotherapy is also defined in accordance with routine perioperative treatment recommendations.③ Dose adjustment rules:Dose modifications for chemotherapy are based on the severity of adverse events per NCI-CTCAE v5.0, including hematologic toxicity, thrombocytopenia, peripheral neuropathy, hepatic dysfunction, renal impairment, and other significant adverse events. For oxaliplatin-related neurotoxicity (grade ≥2), oxaliplatin may be held or reduced by 25%; for grade ≥3, oxaliplatin is discontinued. For thrombocytopenia (platelet <75×10^9^/L), oxaliplatin is held until recovery to ≥100×10^9^/L; for grade 3–4 thrombocytopenia, the dose is reduced by 25% upon re-administration. For S-1 or capecitabine, dose adjustments are based on gastrointestinal toxicity, hand-foot syndrome, and myelosuppression, using standard dose reduction levels (100% → 75% → 50% → discontinuation).Immunotherapy dose modifications follow current international consensus guidelines and the prescribing information for each immune checkpoint inhibitor, with corticosteroid management for immune-related adverse events as per standard practice, e.g., hold for grade 2 pneumonitis/colitis; discontinue permanently for grade 3 or higher. All dose modifications will be recorded prospectively.”Concomitant Medications: Supportive care will be provided to all patients according to clinical oncology guidelines. The use of other Chinese herbal decoctions with purported similar effects, anti-tumor Chinese herbal injections, Chinese patent medicines, thymic peptides, or other immunomodulatory biological agents is prohibited during the study period. Any changes in concomitant medications will be recorded.

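### The stratum used in randomization is not tied to the primary EFS log-rank test or hazard ratio; stratifying both is a small improvement at almost no cost

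*Protocol article*

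**What the plan says.** Section 2.3 (Randomization method): "This trial was stratified by neoadjuvant chemotherapy ± immunotherapy using stratified block randomization". The Abstract and section 2.1 name the same single factor. Section 2.6 (Interventions) gives every participant neoadjuvant chemotherapy: "The preoperative phase will consist of 2–4 cycles of neoadjuvant SOX or XELOX chemotherapy, with or without immunotherapy". What separates the strata is therefore, in effect, whether immunotherapy is planned.

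Section 2.9 (Statistical analysis) names the test for EFS, DFS and OS: "Time-to-event endpoints (EFS, DFS, OS) will be summarized using Kaplan-Meier survival curves and compared between groups using the log-rank test". Two further sentences bear on adjustment: "Prespecified subgroup analyses based on randomization stratification factors, and multivariable adjustment will be used to minimize the influence of treatment heterogeneity" and "The Cox proportional hazards model will be employed for multivariate analysis to adjust for potential confounding variables". The covariates of that Cox model are not listed there. Immunotherapy use and clinical stage do appear in a list of variables with forced entry, but in the subgroup paragraph, which is declared exploratory.

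No section mentions a stratified log-rank test or a stratified Cox model. None says that the test is unstratified either.

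**The concern.** Blocking within strata balances the arms within each stratum. If the stratum predicts EFS, this removes part of the chance variation between the arms. A log-rank test that ignores the stratum still counts that variation in its variance. The test statistic is then too small on average: the true error rate falls below 5%, some power is lost, and the HR is drawn somewhat towards 1.

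The EFS test matters beyond its own result, because section 2.9 allows formal testing of OS, DFS and the recurrence rates only if EFS is significant. The test that opens this sequence should be stated without ambiguity and should follow the allocation scheme.

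There is a second ambiguity. Section 2.6 also allows immunotherapy after surgery, which can be decided after randomization. The immunotherapy-use variable in the subgroup list is therefore not clearly the stratum as randomized.

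**Working it through.** **What the text links.**

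| Element | Section | Linked to the stratum? |
|---|---|---|
| Randomization | 2.3 | Yes, stratified blocks |
| Subgroup analyses | 2.9 | Yes, by name |
| Log-rank test for EFS | 2.9 | No |
| Cox model | 2.9 | Not by name; covariates unspecified |

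**Inputs from the document.** Section 2.5: 3-year EFS 44% against 64%, two-sided alpha 0.05, power 80%, 1:1 allocation, 36 months of accrual, 5 years in total, 114 per group before dropout. Under exponential survival the planned HR is ln(0.64)/ln(0.44) = 0.544.

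**Choice of sample size for the check.** Schoenfeld's formula gives 4 × (1.960 + 0.842)² / (ln 0.544)² ≈ 85 events. With 36 months of accrual in a 60-month trial, the average event probability is 0.503, so about 85 patients per group are needed. The plan's 114 per group does not reproduce from these inputs; it would give about 115 events and about 90% power. That is a separate matter and does not affect this point. The comparison was run at 164 patients in total (close to 80% power) and at 228 (2 × 114).

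**Assumptions not in the document.** Blocks of 4; immunotherapy stratum 30% or 50% of patients; stratum HR from 1.0 to 0.33; exponential survival; no dropout. The overall control 3-year EFS is held at 44%, and the treatment HR within each stratum is 0.544.

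**Statistics compared.** With g the arm indicator (0 or 1) and p the experimental arm's share of those at risk at each event, U = Σ(g − p) and V = Σp(1 − p).
- Plain test: Z = U/√V.
- Stratified test: Z = (U₁ + U₂)/√(V₁ + V₂), summed over the two strata.
- Both reject when |Z| > 1.96.

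**Results at 164 patients, 12,000 runs per cell.**

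| Share | Stratum HR | Error rate, plain | Error rate, stratified | Power, plain | Power, stratified | Loss of plain test (points) |
|---|---|---|---|---|---|---|
| 30% | 1.0 | 0.051 | 0.050 | 79.1% | 78.6% | −0.5 |
| 30% | 0.7 | 0.048 | 0.051 | 78.0% | 78.3% | 0.4 |
| 30% | 0.5 | 0.041 | 0.048 | 77.1% | 78.8% | 1.6 |
| 30% | 0.33 | 0.037 | 0.050 | 75.1% | 79.1% | 4.0 |
| 50% | 1.0 | 0.051 | 0.051 | 78.3% | 77.9% | −0.4 |
| 50% | 0.7 | 0.048 | 0.052 | 78.1% | 78.6% | 0.4 |
| 50% | 0.5 | 0.041 | 0.049 | 76.5% | 78.5% | 2.0 |
| 50% | 0.33 | 0.032 | 0.050 | 72.8% | 79.1% | 6.4 |

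The simulation standard error is about 0.2 points for an error rate and 0.4 points for a power.

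**Results at 228 patients, 50% share, 6,000 runs per cell.** Power, plain against stratified:
- stratum HR 0.79: 90.4% and 90.5%
- stratum HR 0.7: 89.6% and 89.7%
- stratum HR 0.5: 88.5% and 89.8%
- stratum HR 0.33: 85.8% and 90.4%

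For a stratum HR of 0.7 to 0.79 the difference at this size is 0.15 points or less, within simulation error.

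**The only figure in the document near a stratum effect.** The Introduction cites 2-year EFS of 67% against 59% in another trial: ln(0.67)/ln(0.59) = 0.76. If the stratum HR were that, the loss would be under 1 point.

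**The case against.** **Silence is not a decision.** A reader might infer that the plan has chosen an unstratified test. The text does not support that: it says only "compared between groups using the log-rank test". This is a condensed article, and whether a log-rank test is stratified is often settled in the full protocol or analysis plan. That part of the objection stands. What remains is that section 2.9 does assign the stratification factor a place, in the subgroup analyses, and does not connect it to the primary test or HR. The section is specific elsewhere (forced entry, Schoenfeld residuals, fixed-sequence testing), so the plain test is the natural reading.

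**Adjustment is already planned.** It is, but with unnamed covariates and no link to the primary comparison. The forced-entry list belongs to exploratory analyses.

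**The stratum may not be prognostic.** A reader might take the 67% against 59% as showing that it is. It does not. That is the randomized effect of adding durvalumab to FLOT in another trial. Here immunotherapy is limited to biomarker-selected patients and the chemotherapy is SOX or XELOX, so the stratum mixes treatment with tumour biology and its effect could be weaker or stronger. The test is conservative only as far as the stratum is prognostic.

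**The error is on the safe side.** True. The plain test never exceeded the nominal level beyond simulation error.

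**Stage would add more.** A reader might want clinical stage in the primary model as well. The document gives no stage effect from which to size a gain, and stage is not a randomization factor. Taking the p-value from a test stratified on immunotherapy and the HR from a model that also adjusts for stage would let the p-value and the confidence interval disagree.

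**Conclusion.** The point holds as a minor improvement. Randomization is stratified, and section 2.9 does not carry the stratum into the primary test or HR. If the test is run as written, the consequence is a small loss of power that depends on a quantity the document does not give: under 1 point for a stratum HR near 0.7 to 0.8, about 1.6 to 2 points at 0.5, and about 4 to 6 points at 0.33. These figures rest on the assumed immunotherapy share, block size and exponential survival listed above. The validity of a positive result is not in question. If the stratum has no effect, stratifying costs about 0.4 to 0.5 points in the simulation, close to its standard error.

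**What to change.** Add to section 2.9: the primary analysis of EFS is a two-sided log-rank test at the 0.05 level in all randomized patients, stratified by the randomization stratum as recorded in the randomization system and not by immunotherapy eventually received. The HR and its 95% confidence interval come from a Cox model stratified in the same way. OS is analysed likewise.

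If adjustment for baseline clinical stage is wanted, prespecify it as a supportive Cox analysis, so that the primary p-value and HR rest on the same model. If a fuller document already specifies a stratified test, section 2.9 need only say so.

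The cost is a sentence or two. No further data or patients are needed, because the stratum is already held in the randomization system. The change can still be made cleanly: section 3 reports 61 participants recruited and no analysis performed.

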## Trial status and progress

3

Funding sources: the Noncommunicable Chronic Diseases–National Science and Technology Major Project (Grant Nos. 2024ZD0521301 and 2024ZD0521300), 2024.12-2028.11.

Recruitment start date: November 1, 2025; expected completion: August 30, 2028.

Expected primary analysis completion: December 2030.

Expected primary results publication: anticipated in 2031 after completion of follow-up.

Number of recruited participants at submission: 61 (as of 2026.7.9).

Data collection is ongoing at the time of protocol submission; no data analysis has been performed.

## Discussion

4

This trial protocol aims to answer the following primary question: LAGC patients receiving perioperative chemotherapy (± immunotherapy), does the addition of SQFWG improve EFS compared with placebo? We hypothesize that SQFWG will reduce postoperative recurrence and metastasis by modulating immune function and tumor metabolism. The expected findings include a clinically meaningful improvement in 3-year EFS, acceptable safety, and identification of patient subgroups that may derive greater benefit. This protocol emphasizing that results are not yet available, and the statements herein reflect the planned hypothesis and expected outcomes, to test a hypothesis, not to confirm efficacy.

This high recurrence in LAGC is closely associated with postoperative minimal residual disease, an immunosuppressive tumor microenvironment, and immune escape mechanisms, highlighting the limitations of perioperative chemotherapy alone for achieving curative control. Consequently, exploring novel combination therapies with synergistic effects is a crucial strategy for mitigating recurrence and metastasis in LAGC. In this context, the role of TCM in modulating immunity and exerting anti-tumor effects in GC is increasingly recognized.

This view is strongly supported by a recent meta-analysis demonstrating that adding *Atractylodes macrocephala*-containing TCM to neoadjuvant chemotherapy for LAGC significantly improves tumor response. Specifically, this combination increased the objective response rate by 41% (RR: 1.41) and the disease control rate by 20% (RR: 1.20), while also enhancing quality of life (MD: 8.47) and reducing chemotherapy-induced adverse reactions (36). Notably, the analysis revealed that such TCM regimens increased the proportions of peripheral CD3+, CD4+, and CD8+ T-cells, suggesting a reversal of the immunosuppressive tumor microenvironment, a key factor in preventing postoperative recurrence and metastasis in LAGC. These robust findings underscore the therapeutic potential of TCM as an adjunct to modern perioperative chemotherapy, particularly for enhancing immune function and treatment efficacy. Aligned with this evidence, our study introduces SQFWG, a refined hospital preparation derived from the original Chinese herbal compound Weifufang compound developed by [name], and all preclinical and clinical studies cited under the name Weifufang refer to the same fundamental formula.

Our prior research has systematically evaluated the clinical value and potential mechanisms of this formula. Clinical evidence indicates that Weifufang combined with chemotherapy significantly prolongs OS by 3.23 months (13.33 vs. 10.1) in LAGC, improves 1- to 3-year survival rates, enhances QoL (assessed by the QLQ-C30 questionnaire), alleviates cancer-related fatigue (Piper Fatigue Scale), and reduces myelosuppression and gastrointestinal reactions (32–35). Preclinical studies *in vitro* and *in vivo* have revealed that its antitumor effects may involve the regulation of multiple signaling pathways. The formula can upregulate the expression of PPARγ and PTEN while downregulating proliferation-related proteins such as PTTG, c-Myc, and hTERT, thereby inhibiting GC cell proliferation and inducing apoptosis. Additionally, it suppresses the HIF-1α/VEGF pathway, suggesting anti-angiogenic properties (22–29). Network pharmacology analyses (30) predicted that multiple active components of Weifufang may act on targets including TP53, STAT3, and Akt. Subsequent *in vitro* experiments confirmed its ability to inhibit the PI3K/Akt pathway, leading to suppressed cancer cell proliferation. Non-targeted metabolomics (31) further demonstrated that Weifufang inhibits tumor growth in SGC-7901 subcutaneous xenograft models, an effect associated with the modulation of key metabolic pathways such as arginine/proline, nicotinate/nicotinamide, and phenylalanine/tyrosine/tryptophan metabolism, indicating that amino acid metabolic reprogramming is a potential mechanism of action.

Therefore, integrating SQFWG into the perioperative chemotherapy regimen represents a logical next step to test whether its immunomodulatory and metabolic effects can translate into improved EFS, reduced postoperative recurrence, and better outcomes for LAGC patients. We will conduct that multicenter, large-sample, prospective randomized controlled trial to obtain more clinical evidence-based data. By analyzing patient serum samples and building on previously identified differential metabolites, we aim to elucidate the molecular mechanisms through which this formula modulates tumor metabolism and to clarify its pharmacodynamic material basis.

Therefore, our clinical trial is designed to evaluate the clinical efficacy of integrating TCM into perioperative therapy for reducing postoperative recurrence and metastasis in LAGC. Key strengths of the trial design include: (1) the use of an Interactive Web Response System for centralized randomization with allocation concealment, which balances unmeasured confounders across multiple participating centers; (2) implementation of blinding for participants, investigators, outcome assessors, and statisticians to minimize placebo effects, information bias, and performance bias, thereby enhancing data validity; (3) administration of the TCM intervention throughout the entire perioperative period alongside chemotherapy ± immunotherapy, with strict control of concomitant medications; and (4) The use of placebo (5% SQFWG) at low concentration of the original drug is in accordance with the “*Criteria for Simulated Effect Evaluation of Placebo in Chinese Patent Medicine*” (T/CACM 1420-2022) issued by the Chinese Society of TCM, which can ensure the feasibility of ethics and trial implementation. We have nevertheless acknowledged that residual biological activity cannot be completely excluded and that such activity would be expected to bias the results toward the null hypothesis, resulting in a more conservative estimate of treatment efficacy. If any minimal biological activity exists, a positive finding would be even more robust. Furthermore, we will conduct a *post-hoc* blinding assessment using the Bang Blinding Index; if substantial unblinding occurs, we will perform sensitivity analyses to evaluate potential bias. In terms of sample size, this is a large expected effect for an adjunctive herbal intervention in the context of modern perioperative therapy, we will interpret clinical effect results with greater caution. We acknowledge that our prior studies of Weifufang (the precursor formulation of SQFWG) were small, single-center, and predominantly non-randomized, and thus provide hypothesis-generating rather than confirmatory evidence.

This protocol outlines a scientifically rigorous, clinical trial. By implementing a multicenter enrollment strategy in China and employing EFS as a robust primary endpoint, the study aims to evaluate the clinical efficacy and safety of SQFWG combined with neoadjuvant chemotherapy ± immunotherapy in reducing postoperative recurrence and metastasis in LAGC. It further seeks to identify patient subgroups most likely to benefit and to explore the underlying mechanisms of efficacy. The findings are expected to provide evidence-based support for integrating TCM into the comprehensive perioperative management of LAGC, refine its role within modern treatment strategies, optimize the application framework for herbal formulations, and establish a foundation for precise clinical use.

